### Primary outcomes

Global cognitive factor scores, the primary outcome measure, will be calculated using cognitive test data from the LASI-DAD battery, administered at baseline, and 12, 24, and 36 months later. The LASI-DAD battery of cognitive and neuropsychological tests assesses several domains of cognitive function and has been validated for use in India, including in Telangana [25, 26].

### Secondary outcomes

These include 36-month change in quality of life using the World Health Organization Quality of Life Brief Version (WHOQOL-BREF) [27], visual functioning (21-item Rasch version of the Indian Vision Function Questionnaire) [28], depression (Patient Health Questionnaire-9) [29], physical activity (International Physical Activity Questionnaire) [30], social interaction and networking (Social Networking Index questionnaire) [24], and falls risk (Quick Screen falls assessment) [31]. The trial will also assess the cost-effectiveness of the intervention as total intervention cost per quality-adjusted life years gained in the intervention group. The Client Service Receipt Inventory will be used to assess the resource use for medical care by the study participants [32] (Table 1).

**Table 1 Tab1:** Schedule of assessments with details on location, personnel, and frequency

	Instrument name	Details	Baseline	Year 1	Year 2	Year 3
1	Personal and demographic information questionnaire	It includes age/gender, level of education, marital status, and income	✓			
2	World Health Organization Quality of Life Brief Version (WHOQOL-BREF) [27]	It has 26 items and covers four domains of quality of life: a) physical health, b) psychological well-being, c) social relationships, and d) environment	✓	✓	✓	✓
3	Indian Vision Function Questionnaire [28]	It has 20 questions covering visual functioning and mobility domains	✓	✓	✓	✓
4	Patient Health Questionnaire (PHQ9) for depression [29]	It has nine questions with scores of 0–3 points per question, for a total score of 0–27 points	✓	✓	✓	✓
5	Social Networking Index questionnaire [24]	It has 12 questions that assess the number of high-contact roles (network diversity), number of people in social networks, and embedded networks	✓	✓	✓	✓
6	International Physical Activity Questionnaire (IPAQ) Short form [30]	It has 7 questions and measures a 7-day recall of physical activities	✓	✓	✓	✓
7	Risk factors (alcohol consumption and smoking)	Includes questions on present and past smoking and alcohol consumption	✓	✓	✓	✓
8	Hindi Mini mental State Examination (HMSE) [19]	It is a 22 questions-based scale with a maximum score of 31	✓			
9	Ocular history and systemic health questionnaire	It includes questions on previous surgeries, use of spectacles, and duration of use. Systemic health questionnaire includes information on hypertension, diabetes and other non-communicable diseases	✓	✓	✓	✓
10	Longitudinal Aging Study in India–Diagnostic Assessment of Dementia; LASI-DAD cognitive test battery [25, 26]	It covers the key cognitive domains: memory, attention/speed, orientation, language function, visuospatial skills, executive function, numerical ability, and retrieval fluency	✓	✓	✓	✓
11	Client Service Receipt Inventory for healthcare costs [32]	This collects information on the whole range of services, including estimating the costs of service receipt	✓	✓	✓	✓
12	Clinical Falls Risk Assessment: Quick screen questionnaire [31]	It assesses five factors related to falls: history of falls in the last 12 months, regular use of four or more medications, vision, peripheral sensation, balance, time reaction, and lower limb strength	✓	✓	✓	✓

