Three-year change from baseline in quality of life, visual functioning, depression, falls, social interaction and networking, and physical activity will be the secondary outcomes. Rasch analysis will be conducted to derive interval scores from quality of life and vision-related quality-of-life instruments. A mixed-effects binomial regression with a log link will be used to estimate the relative risk, and a binomial model with an identity link for estimating the risk difference will be used to assess between-group differences in change in depression. A mixed-effects linear regression with an identity link will be used to estimate the between-group mean difference in change in falls. Participants will be placed into three categories of physical activity and social interaction for these analyses as previously described [30, 34].

The cost-effectiveness analysis will estimate the expected incremental cost per unit difference in the cognitive factor scores between the intervention and the control groups. A health and social care perspective will be used for the analysis. A Markov model will be developed, allowing the comparison of the CLEVER intervention with alternative interventions for preventing cognitive decline. An “in-trial” analysis that compares the costs and outcomes of the two study groups for the time horizon of the trial will be conducted. Multinomial logistic regression will be used to adjust for potential confounders. Odds ratios and their 95% confidence intervals will be reported.

Statistical significance of all results will be assessed at the conventional level of *p* < 0.05 (two-tailed). Stata (V.16, Stata Corp, College Station, Texas, USA) will be used for all statistical analyses.

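### The article defines cost-effectiveness in two unreconciled ways, and the definition under Secondary outcomes is not a between-group ratio

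*Protocol article*

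**What the plan says.** Cost-effectiveness is one of the trial's stated aims (Background, last paragraph). The protocol article then defines it twice.

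- **Secondary outcomes:** cost-effectiveness will be assessed "as total intervention cost per quality-adjusted life years gained in the intervention group". The same paragraph adds that "The Client Service Receipt Inventory will be used to assess the resource use for medical care by the study participants", and Table 1 schedules that inventory at baseline and Years 1 to 3.
- **Data management and analysis plan:** the cost-effectiveness analysis "will estimate the expected incremental cost per unit difference in the cognitive factor scores between the intervention and the control groups". It continues: "A health and social care perspective will be used for the analysis". An analysis within the trial's time horizon is to set one group's costs and outcomes against the other's. In addition, "A Markov model will be developed, allowing the comparison of the CLEVER intervention with alternative interventions for preventing cognitive decline". QALYs are not mentioned in this section.

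On quality of life, Table 1 describes the WHOQOL-BREF thus: "It has 26 items and covers four domains of quality of life". The analysis section adds: "Rasch analysis will be conducted to derive interval scores from quality of life and vision-related quality-of-life instruments".

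**The concern.** A reader who goes to the outcomes section and a reader who goes to the analysis section would compute different quantities and call both the trial's cost-effectiveness result. If nothing says that both are planned, or which leads, the choice can be made after the data are seen.

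The outcomes-section ratio has a further problem. A cost-effectiveness ratio should say what the intervention adds in cost and in benefit relative to the comparator. Intervention cost divided by a gain within the intervention group does neither: it takes no account of differences in other care costs, and it does not subtract the change that occurs among controls. This matters here because controls receive a prescription at baseline and are not prevented from obtaining spectacles on it (Controls; Intervention), so a control-group gain of zero cannot be taken for granted.

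**Working it through.** The article gives no economic figures, so there is no plan figure to reproduce. The check compares the two definitions and then looks at when they could agree.

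**Side by side**

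| | Secondary outcomes | Data management and analysis plan |
|---|---|---|
| Numerator | Total cost of the intervention | Incremental cost, from a health and social care perspective |
| Denominator | QALYs gained | Difference in cognitive factor score |
| Comparator | None named; refers to the intervention group | Control group |

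The definitions differ on all three elements. Neither section mentions the other's effect measure or refers to the other.

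**When the outcomes-section ratio would equal an incremental cost per QALY**

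Per participant, let S be the intervention cost, O_I and O_C the other care costs in the two groups, and Q_I and Q_C the QALYs gained.

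- Outcomes section as written: S / Q_I
- Incremental cost per QALY: (S + O_I − O_C) / (Q_I − Q_C)

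In general these agree only if other care costs are equal (O_I = O_C) and controls gain no QALYs (Q_C = 0), apart from chance offsets between the two. The article supports neither condition. Its Client Service Receipt Inventory would inform O_I and O_C, and a numerator of intervention cost alone would make no use of it. Even if both conditions held, the result would be per QALY, whereas the analysis section's ratio is per unit of cognitive factor score. The two are on different scales.

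**Illustration of the numerator alone**

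All figures here are assumed; none comes from the article. Take S = 20, O_C = 100 and a QALY gain of 0.02, used as the denominator of both ratios so that only the numerators differ.

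| O_I | Outcomes section: 20 / 0.02 | Incremental: (20 + O_I − 100) / 0.02 |
|---|---|---|
| 80 | 1,000 | 0 / 0.02 = 0 |
| 100 | 1,000 | 20 / 0.02 = 1,000 |
| 120 | 1,000 | 40 / 0.02 = 2,000 |

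The first ratio does not respond to other care costs; the second does. This shows the mechanism and is not a forecast.

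**Source of QALYs**

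Table 1 has 12 rows: demographics, WHOQOL-BREF, Indian Vision Function Questionnaire, PHQ-9, Social Networking Index, IPAQ, smoking and alcohol, HMSE, ocular and systemic history, LASI-DAD, Client Service Receipt Inventory, and the falls screen. None is described as preference-based. Rasch interval scores, planned for the quality-of-life instruments, are not health-state utilities. The Markov model is mentioned without a source of utilities.

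**The case against.** The best defence is that the outcomes-section sentence is a loose one-line summary and that the analysis section governs. That section is explicitly incremental, states a perspective and compares both groups. The inventory is not limited to one group, and the word for gain can be read as relative to a comparator. A trial may also properly report both a cost per QALY and a cost per unit of cognition, and the plan for a Markov model alongside an in-trial analysis makes two outputs plausible.

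Much of this stands. The economic plan as a whole does not ignore the control group, and the two effect measures are not mutually exclusive. What the defence does not supply is any sentence saying that two ratios are planned or which is main. Nor does it remove the wording that ties the ratio to intervention cost and to the intervention group.

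A reader might infer more than the document supports:

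- *That the cost per QALY cannot be computed.* Utilities could come from a mapping, from external values in the Markov model, or from a fuller health-economics plan that is not shown. All that can be said is that the article names no source.
- *That the two definitions would lead to opposite conclusions, or differ by some known factor.* The article gives no costs, utilities or decision threshold. Any factor would come from the figures assumed, and the two ratios have different units.
- *That QALYs should be demoted or dropped.* That choice belongs to the investigators; the document supports only aligning the definitions.
- *That leaving out spectacles bought privately by controls is an error in costing.* Whether they count depends on the perspective, and a health and social care perspective does not clearly include them. Their effect on control outcomes matters either way.

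**Conclusion.** The point holds as an unreconciled definition of a secondary outcome. The two sections specify ratios that differ in numerator, denominator and comparator. The one under Secondary outcomes, followed literally, is not incremental and conflicts with the analysis section's two-group comparison and stated perspective. The size of the effect on the result cannot be derived from the article, and the illustration shows direction only.

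The conclusion rests on the article's wording alone. If a fuller health-economics plan already fixes a single incremental definition and a source of utilities, what remains is to correct the published sentence. Because cost-effectiveness is a stated aim and the repair is cheap, it should be made before the analysis, which is scheduled for the end of the trial.

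**What to change.** 1. Reword the sentence under Secondary outcomes as a between-group incremental ratio: (mean cost, intervention − mean cost, control) / (mean effect, intervention − mean effect, control). Costs follow the stated health and social care perspective: service use from the Client Service Receipt Inventory plus the costs of the intervention.
2. Use the same definition in the Data management and analysis plan section. State which effect measure is main: cognitive factor score, QALY, or both in a stated order.
3. If QALYs are kept, name the source of utilities, whether a mapping, external values for the model, or a preference-based instrument added to Table 1.

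Cost: wording in the protocol and in any health-economics plan. No new data are needed unless directly measured utilities are wanted, which would mean adding an instrument to the remaining visits. The primary outcome, its analysis and the sample size of 760 do not change.

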### Study team

A multidisciplinary team, including vision care professionals (ophthalmologist, optometrists and vision technicians), neuropsychologists and psychologists, social investigators, and community eye health workers will conduct this trial. The logistics of the trial, including appointments, management of the trial site, treatment allocation based on clinical trial unit (CTU) recommendation, and tracking of spectacles compliance, will be organized by a trial coordinator. The principal investigators ([name]) are responsible for the scientific and administrative aspects of the trial, with the support of the TMG.

### Interviews

Trained investigators will conduct personal interviews in the participant’s native language (Telugu or Hindi). Adequate time will be allotted for participants to rest between assessments. The same investigator will conduct the entire interview for each participant.

### Clinical examination

This includes the following components, 1) external examination (including ocular motility and alternate cover test); 2) assessment of monocular near (using a logarithm of minimum angle of resolution [logMAR] chart at 40 cm) and distance visual acuity (VA, unaided, best-corrected, pinhole, and with existing spectacles if available, with a logMAR chart at 3 m using tumbling E optotypes, at an illumination of ≥ 180 lx measured with a light meter); 3) objective and subjective refraction, for participants with presenting distance VA worse than 6/9 or near VA worse than N6 in either eye; 4) slit-lamp biomicroscopy and assessment of the lens status after pupil dilation (SL 120 Carl Zeiss Meditec, Inc., Dublin, CA); 5) applanation tonometry (Carl Zeiss Meditec, Inc., Dublin, CA); 6) fundus examination and imaging with pupil dilation. In addition, seven field fundus photographs (Centervue, Italy) and lens photography with optical section and retro illumination view on a slit lamp camera (Haag-Streit Imaging module 910, Haag-Streit, Switzerland) will be captured. Retinal Optical Coherence Tomography (Cirrus Optical Coherence Tomographer, Carl Zeiss Meditec, Jena, Germany), with 5-line raster and macular cube will be performed on all participants.

Serum haemoglobin A1C (HbA1C) levels will be assessed on all participants (NycoCard reader, Abbott Diagnostics Technologies AS, Oslo, Norway) to assess blood glucose control over recent months. Inter-examiner reliability will be assessed for measurement of VA and refraction. Pilot testing of all examination procedures will be carried out with 20 eligible participants before beginning the main trial.

### Cognitive examination

The complete LASI-DAD neuropsychological test battery will be performed in the Telugu or Hindi languages. It assesses the following domains, 1) Orientation (Community Screening Instrument for Dementia); 2) visuospatial (constructional praxis); 3) language fluency (retrieval fluency); 4) immediate and delayed memory (word recall); 5) executive functions (Go-No-Go task); and 6) decision-making and judgment (judgement and problem-solving) [25, 26]. Psychologists will be trained to administer the cognitive test battery on patients and healthy older adults at the National Institute of Mental Health & Neuro Sciences (NIMHANS) under the supervision of the Clinical Psychologist/Neuropsychologist before performing the assessments on participants in the pilot and main trial.

### Intervention

All participants in the intervention group will receive free near and/or distance spectacles plus instructions on their use within two weeks of the examination, with annual replacement in case of loss, breakage or change in power such that VA falls below the enrolment criteria. Adherence with use of spectacles will be assessed in both study groups through phone calls made every three months and half yearly home visits. Intervention group participants adherent with spectacle wear will be rewarded through nonfinancial incentives such as vouchers for diagnostic tests and other utility items at regular intervals. There will be no special criteria for discontinuing or modifying allocated interventions. No attempts will be made to prevent control participants from obtaining spectacles outside the study based on the prescriptions provided.

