### Trial design

CLEVER is a single-centre, open-label, parallel-group, individually-randomised controlled trial, designed to test the impact of immediate versus delayed provision of free spectacles on rates of cognitive change among community-dwelling elderly persons.

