### Controls

All participants randomised to the control group will receive a prescription for spectacles at baseline, as is the standard of care in the area, and will receive near and/or distance spectacles at no cost at study closeout.

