### Randomisation, allocation and masking

The randomisation sequence will be generated by the trial statistician in the LVPEI CTU using an online randomisation tool (https://www.sealedenvelope.com). Stratified randomisation will be done based on gender (male/female), age (below and above median), education level (below and above median), and baseline HMSE (below and above median). Group allocation will be concealed from the trial coordinator and field team until a potential participant is determined eligible. Trial personnel will not be masked to participants’ treatment assignment due to practical difficulties in assessing the main trial outcome without study spectacles being worn. Masking of participants with use of zero-power spectacles among controls is not considered ethical in this setting.

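### Rewards, including diagnostic-test vouchers, go only to adherent intervention participants, so the arms differ by more than the timing of free spectacles

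*Protocol article*

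**What the plan says.** The Trial design section describes the trial as "designed to test the impact of immediate versus delayed provision of free spectacles on rates of cognitive change". Rewards are not part of that contrast.

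The Intervention section adds them: "Intervention group participants adherent with spectacle wear will be rewarded through nonfinancial incentives such as vouchers for diagnostic tests and other utility items". They recur ("other utility items at regular intervals"), but the article gives no interval, value, duration or type of test.

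The Controls section says that controls "will receive a prescription for spectacles at baseline, as is the standard of care in the area". Their free pair follows only when the study ends. That section mentions no interim reward, and no reason for the difference appears anywhere in the article.

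Contact is the same in both arms: "Adherence with use of spectacles will be assessed in both study groups through phone calls made every three months and half yearly home visits". The trial is open-label, and "Trial personnel will not be masked to participants’ treatment assignment".

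On costs, the Secondary outcomes section says: "The Client Service Receipt Inventory will be used to assess the resource use for medical care by the study participants".

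**The concern.** In an open-label trial, the between-arm difference can be credited to spectacles only if spectacles are all that differs by design. Here one arm also has a reward scheme, part of which is health care. Three consequences are possible, and they are not equally well supported.

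- **Co-intervention.** A diagnostic test paid for by voucher is itself service use, and its result may lead to more. That bears on the Client Service Receipt Inventory, collected at baseline and in years 1 to 3, and on a cost-effectiveness analysis taken from a health and social care perspective. Quality of life could also move. An effect on cognition is conceivable but needs more steps.
- **Adherence data.** The reward depends on being found adherent. Intervention participants therefore have a reason to overstate wear that controls lack. The secondary per-protocol analysis groups people by treatment actually received, so it is exposed to this.
- **Retention.** Recurring rewards may keep people in the trial, mainly in one arm. This is an inference about effect, because the article ties the reward to wear and not to attendance.

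**Working it through.** **The plan's own figure.** Inputs from the Sample size section and the Abstract: 90% power, two-sided 5%, two-sample t-test, 13% annual loss, effect size 29% (read here as 0.29 SD, an assumption), 380 per arm.

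- n per arm = 2(1.960 + 1.282)² / 0.29² = 250 (normal approximation; the exact t calculation gives 251).
- Retained at three years = 0.87³ = 0.659, a loss of 34.1%.
- 250 / 0.659 = 380 per arm, 760 in total.

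The stated 760 is reproduced, so the sample size is not in dispute. About 250 per arm are expected at 36 months.

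**Comparison of the arms, as written.**

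| Component | Intervention | Control |
|---|---|---|
| Spectacles | free, early | prescription at baseline; free at closeout |
| Three-monthly calls, half-yearly visits | yes | yes |
| HbA1C; yearly systemic health questionnaire | yes | yes |
| Recurring rewards, including diagnostic-test vouchers | if adherent | none |

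The last row is the difference that the stated contrast does not cover.

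**Illustration (a): shift in the primary outcome.** The shifts are assumptions, not figures from the article. With 250 per arm, SE = √(2/250) = 0.0894 SD. If spectacles had no effect and the rewards moved the intervention-arm mean by b, the rejection rate is 1 − Φ(1.96 − b/SE) + Φ(−1.96 − b/SE).

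| b (SD) | share of 0.29 | rejection rate |
|---|---|---|
| 0.03 | 10% | 6.3% |
| 0.05 | 17% | 8.6% |
| 0.10 | 34% | 20.1% |
| 0.15 | 52% | 38.9% |

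Here b is an average over the whole arm. If only a fraction a of the arm is adherent and rewarded, the effect per rewarded person must be b/a, which is larger than b.

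**Illustration (b): unequal retention.** Again the inputs are assumptions. Controls lose the planned 13% a year (250 of 380 retained). The intervention arm loses 10%, 8% or 5% a year, so 0.90³ = 0.729 (277), 0.92³ = 0.779 (296) or 0.95³ = 0.857 (326) are retained. If those lost would have scored D SD worse than those retained, an unadjusted completer comparison is shifted by (r_control − r_intervention) × D:

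- smallest case, 10% loss and D = 0.2: (0.659 − 0.729) × 0.2 = −0.014 SD;
- largest case, 5% loss and D = 0.5: (0.659 − 0.857) × 0.5 = −0.099 SD.

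The sign is against the intervention, so (a) and (b) can act in opposite directions.

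**The case against.** The strongest reply is that adherence support is part of the intervention. It appears under that heading, next to instructions and replacement of spectacles, and an intention-to-treat comparison validly estimates the effect of the whole package. That stands as far as it goes, and it makes part of the problem one of labelling. It does not explain why the reward should be a diagnostic test when non-health items could also encourage wear.

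Other points limit the concern:

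- A reader might infer that the whole intervention arm gets health vouchers for three years while controls get nothing until closeout. The article does not say that. Rewards go to adherent participants, no duration is given, and controls receive a prescription at baseline.
- HbA1C is measured in all participants, and the yearly systemic health questionnaire is not restricted by arm. Some finding of diabetes and hypertension is therefore symmetric, which narrows that route to cognition. The article does not say which tests the vouchers cover or that treatment follows.
- Free spectacles at closeout give controls their own reason to stay.
- Overstated wear reaches only a secondary analysis, and home visits as well as calls are used to assess wear. The article does not say that wear is judged by self-report alone.
- Controls may obtain spectacles elsewhere, so separation between the arms depends on wear in the intervention arm. Removing the wear-contingent reward altogether could weaken the contrast. This is a fair objection to that remedy.

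**Conclusion.** The asymmetry holds and nothing else in the article corrects it. One arm has a recurring reward, possibly including health services, that lies outside the stated contrast. The best-supported consequences are for medical resource use and cost, quality of life, and the adherence data behind the per-protocol analysis. An effect on cognition is less certain, and an effect on retention is inferred.

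A reader might take the 8.6% to 20.1% rejection rates as the trial's actual false-positive risk. The documents do not support that: the figures follow wholly from assumed arm-level shifts of 0.05 to 0.10 SD, and 0.10 SD is about a third of the design effect. Nor can a net bias in favour of spectacles be claimed, since differential retention could act against them. The point is worth correcting because the correction is cheap, not because a large bias has been shown.

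**What to change.** 1. In the Intervention section, replace diagnostic-test vouchers with utility items that have no health-service content.
2. The wear-contingent reward may stay in the intervention arm. In the Controls section, give controls an item of equal value, at the same intervals, for completing the same three-monthly call or half-yearly home visit.
3. In the Trial design section, describe the intervention as spectacles plus adherence incentives.
4. In the cost-effectiveness paragraph, state that the rewards count as an intervention cost. The Secondary outcomes section already refers to total intervention cost and does not exclude them, but this should be explicit.

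The cost is low-value items for up to 380 controls and a protocol amendment. No extra staff or visits are needed, because the contacts already take place in both arms.

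Some asymmetry remains. While the intervention reward depends on wear, the reason to overstate wear stays, and the per-protocol result should be read with that in mind. Rewarding only completed contacts in both arms would remove it, but might reduce wear and so the separation between the arms.
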